## Document history

| Version | Date      | Changes to previous version |
|---------|-----------|-----------------------------|
| 1.0     | 18-Jun-14 |                             |
|         |           |                             |

## 1. INTRODUCTION

This analysis plan describes the ISS analyses planned for the Pyramax paediatric (granule) formulation submission to EMA.

For the analysis of paediatric safety data the safety data of the following studies will be pooled:

- SP-C-003-05, Cohort D, patients treated with the PA granule formulation weighing <20 kg
- SP-C-007-07 (both PA and AL) weighing <20 kg
- WANECAM paediatric patients (weighing <20 kg) from the corresponding sub study analysis, treatment episode 1 only.

All analyses will be performed by DATAMAP GmbH, Freiburg, Germany using SAS®, Version 9.3 in a UNIX environment.

## 2. DEFINITIONS AND DATA CONVENTIONS

### Baseline

Baseline for analysis purpose will be defined as the last measurement prior to first study drug administration, i.e., in general the Day 0 pre-dose assessment.

### Study days

Study days will be calculated as actual date minus date of first study drug intake, i.e. the day of first study drug intake will be defined as Day 0.

### Calculation of age

Age will be calculated from the date of the screening visit and the date of birth and presented as integer value. If the date of birth is not available age as entered on the CRF will be used.

The following SAS code will be used to calculate age where &dob is the date of birth and &dat is the date of visit 1

```
floor((intck('MONTH',&dob,&dat)-(day(&dat)<day(&dob)))/12)
```

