## 5. DEMOGRAPHIC DATA AND BASELINE CHARACTERISTICS

Demographic data and baseline characteristics will be presented by treatment group.

Data will be summarised with number of observations, mean, standard deviation, minimum, median, quartiles, and maximum for continuous variables and with number and percentage of patients for categorical variables.

Continuous variables: age, height, weight, BMI

Categorical variables: sex, ethnicity, age category (<=6 months, >6 months to <1 year, 1 to 2 years, 3 to 5 years, >=6 years), body weight category (5-<8 kg, 8-<15 kg, 15-<20 kg).

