**Table 2.7.4-2**      **Demographic characteristics**  
**Paediatric safety population**  
**(Page 1 of 3)**

| Variable/
Statistic/Category | Pyronaridine
artesunate
(N=xxx) | Artemether
lumefantrine
(N=xxx) |
|---------------------------------|---------------------------------------|---------------------------------------|
| Gender, n (%)                   |                                       |                                       |
| Male                            | xxx (xx.x)                            | xxx (xx.x)                            |
| Female                          | xxx (xx.x)                            | xxx (xx.x)                            |
| Age (years)                     |                                       |                                       |
| Available observations          | xxx                                   | xxx                                   |
| Mean                            | xx.x                                  | xx.x                                  |
| Standard deviation              | x.xx                                  | x.xx                                  |
| Minimum                         | xx                                    | xx                                    |
| Q1                              | xx.x                                  | xx.x                                  |
| Median                          | xx                                    | xx                                    |
| Q3                              | xx.x                                  | xx.x                                  |
| Maximum                         | xx                                    | xx                                    |
| Age category, n (%)             |                                       |                                       |
| <=6 months                      | xxx (xx.x)                            | xxx (xx.x)                            |
| >6 months - <1 year             | xxx (xx.x)                            | xxx (xx.x)                            |
| 1-2 years                       | xxx (xx.x)                            | xxx (xx.x)                            |
| 3-5 years                       | xxx (xx.x)                            | xxx (xx.x)                            |
| >=6 years                       | xxx (xx.x)                            | xxx (xx.x)                            |

Missing values were not included in the calculation of percentages.

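### The SAP's only age derivation returns 0 for every child under 12 months, so it cannot fill the two infant age rows that Section 5 and Table 2.7.4-2 require

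*SAP*

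**What the plan says.** Section 2 (Calculation of age) gives the rule: "Age will be calculated from the date of the screening visit and the date of birth and presented as integer value". It then prescribes SAS code, "floor((intck('MONTH',&dob,&dat)-(day(&dat)<day(&dob)))/12" (closing bracket omitted here), where the two dates are date of birth and visit 1. For children without a date of birth it adds: "If the date of birth is not available age as entered on the CRF will be used". The unit of that CRF age is not stated.

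Section 5 uses age in two ways. It is among the continuous variables ("Continuous variables: age, height, weight, BMI"), and it is also categorised: "age category (<=6 months, >6 months to <1 year, 1 to 2 years, 3 to 5 years, >=6 years". The Table 2.7.4-2 shell follows both uses. It labels age in years, gives the mean to one decimal and the minimum, median and maximum as whole numbers. It has a separate row for each infant category, including ">6 months - <1 year".

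The SAP defines no age in months and no rule for assigning a child to either infant row.

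**The concern.** Two of the five age categories lie below 1 year and are separated at 6 months. A variable that counts completed years has only one value below 1 year. The prescribed derivation and the prescribed table therefore conflict, and a programmer who follows Section 2 exactly has no way to fill the two rows correctly.

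At stake is the count of the youngest children exposed. The plan pools safety data for a granule formulation in children under 20 kg (for example "SP-C-007-07 (both PA and AL) weighing <20 kg"), and the authors themselves chose to split infants at 6 months. Without a stated rule, two programmers could report different counts, above all for children in their seventh month of life.

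**Working it through.** **Inputs.** The age expression and the CRF fallback come from Section 2, the categories from Section 5, and the layout from Table 2.7.4-2. The SAP states no figure to reproduce and no age distribution, so the distributions in step 3 are assumptions.

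**Step 1: what the expression does.**

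m = (month boundaries between birth and visit) − 1 if the day of the month at the visit is earlier than at birth, otherwise − 0

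age = floor(m / 12)

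Here m is age in completed months. The division and floor turn it into completed years.

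**Step 2: all birth dates in the first year of life.** With a visit date of 15 June 2013 (arbitrary), the expression was evaluated for birth dates 0 to 365 days earlier. All 365 dates from 0 to 364 days gave 0. The value 1 first appeared at day 365, the first birthday. Examples:

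| Born | m | SAP age | Row the child belongs in |
|---|---|---|---|
| 15 Mar 2013 | 3 − 0 = 3 | floor(0.25) = 0 | up to 6 months |
| 16 Dec 2012 | 6 − 1 = 5 | floor(0.42) = 0 | up to 6 months |
| 15 Dec 2012 | 6 − 0 = 6 | floor(0.50) = 0 | up to 6 months (exactly 6) |
| 14 Dec 2012 | 6 − 0 = 6 | floor(0.50) = 0 | over 6 months (by 1 day) |
| 20 Nov 2012 | 7 − 1 = 6 | floor(0.50) = 0 | over 6 months (by 26 days) |
| 16 Jun 2012 | 12 − 1 = 11 | floor(0.92) = 0 | over 6 months |
| 15 Jun 2012 | 12 − 0 = 12 | floor(1.00) = 1 | 1 to 2 years |

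The SAP age is the same in both infant rows. From 1 year upwards, completed years assign the remaining three categories correctly.

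The third to fifth lines also show that dropping the floor and classifying on completed months would not be enough. All three children have m = 6, yet only the first is at or below 6 months.

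**Step 3: continuous age.** Mean exact age (days/365.25) was compared with mean SAP age in 200,000 simulated children for each assumed distribution:

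| Assumed ages (years) | Exact mean | SAP mean | Shortfall | Share of exact mean |
|---|---|---|---|---|
| Uniform 0.5 to 7 | 3.749 | 3.232 | 0.517 | 13.8% |
| Uniform 0.25 to 8 | 4.130 | 3.619 | 0.511 | 12.4% |
| Normal, mean 3.5, SD 1.5 | 3.509 | 3.014 | 0.495 | 14.1% |
| Normal, mean 2.5, SD 1.2 | 2.515 | 2.023 | 0.493* | 19.6% |
| Triangular 0.25, 5, 8 | 4.415 | 3.916 | 0.499 | 11.3% |

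*Computed before the means were rounded. The normal distributions were limited to 0.25 to 9 years.

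The shift is stable at 0.49 to 0.52 year. The percentage, 11% to 20%, depends on the assumed ages. With completed months/12 in place of completed years, the shortfall is 0.040 year in every case, about half a month.

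**The case against.** The strongest reply is that nothing is lost from the data. Date of birth and visit 1 date are both inputs to the code, its numerator is already age in completed months, and the category labels are given in months. A competent programmer would see that the infant rows need a finer age, and the reference to an integer can be read as describing how age is displayed. This stands to the extent that the infants can be separated from the data. It does not remove the conflict: the floor is inside the code prescribed for calculating age, and a programmer who departs from it must still choose a convention at 6 months that the SAP does not supply.

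A reader might infer that all infants will be counted in the youngest row, because 0 satisfies the limit of 6 months. The document does not direct this. It would mean comparing a value in years with a limit in months, and the second infant row would always be empty.

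A reader might also infer that mean age is biased. Completed years is a usual convention, the SAP discloses it, and the shell's unit and whole-number minimum, median and maximum agree with it. The half-year difference is a loss of precision relative to exact age.

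Finally, the reach is small. Safety subgroups are formed by body weight category, and the SAP does not say how many infants there are.

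**Conclusion.** The point holds as a conflict between a prescribed derivation and a prescribed output. The age variable in Section 2 is 0 for every child under 12 months with a known date of birth, so it cannot fill the two infant rows of Table 2.7.4-2. This follows from the code alone and rests on no assumption. For children without a date of birth, whether the rows can be filled depends on a CRF unit that the SAP does not give.

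The stronger readings, that the infant count is necessarily overstated or that the infants cannot be separated at all, go beyond the document.

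The shortfall of about 0.5 year in continuous age assumes birthdays spread roughly evenly over the year of age. It matters more in children under 20 kg than it would in adults, but it remains a question of precision.

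Only Table 2.7.4-2 and the age printed in the SAE listing are affected. No adverse event rate, liver analysis, body weight subgroup or p-value changes. It should be corrected before the tables are run, because the cost is low and the infant count otherwise rests on an unstated choice.

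**What to change.** 1. **Infant rows.** Classify directly from the two dates. For example, a child belongs in the youngest row if visit 1 falls on or before the date of birth plus 6 calendar months, and otherwise in the second row if visit 1 falls before the first birthday. State the convention for birth dates whose day does not exist in the later month.
2. **Older rows.** Keep completed years, as now coded, for 1 to 2, 3 to 5 and 6 years or older.
3. **Missing date of birth.** State the unit of the CRF age and how it maps to the rows. If months are not recorded, count the child as missing for the infant split and report how many there are, for instance in a footnote.
4. **Continuous age (optional, cheap).** Summarise completed months/12 to one decimal, or age in months.

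Items 1 to 3 cost about a line or two of SAS and a few sentences in Section 2. Item 4 also needs a small change to the number formats, or the unit, in the Table 2.7.4-2 shell.

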### Calculation of Body Mass Index (BMI)

BMI will be calculated as weight (kg) / [height (m)]

BMI will be rounded to one decimal.

### Labelling of treatment groups

Treatment groups will be labelled

Pyronaridine artesunate (if necessary, the abbreviation PA will be used)

Artemether lumefantrine (if necessary, the abbreviation AL will be used)

## 3. ANALYSIS POPULATION

All patients from the above studies who received at least one dose of study drug will be included in the paediatric safety population.

## 4. PATIENT DISPOSITION

Patient disposition will be summarised with the number and percentage of patients who were randomized, treated, who discontinued the study prematurely by treatment group and overall. Further, the reasons for premature discontinuation from the study will be summarised.

## 5. DEMOGRAPHIC DATA AND BASELINE CHARACTERISTICS

Demographic data and baseline characteristics will be presented by treatment group.

Data will be summarised with number of observations, mean, standard deviation, minimum, median, quartiles, and maximum for continuous variables and with number and percentage of patients for categorical variables.

Continuous variables: age, height, weight, BMI

Categorical variables: sex, ethnicity, age category (<=6 months, >6 months to <1 year, 1 to 2 years, 3 to 5 years, >=6 years), body weight category (5-<8 kg, 8-<15 kg, 15-<20 kg).

## 7. EXPOSURE TO STUDY DRUG / CONCOMITANT TREATMENTS

The following will be summarized:

- Number and percentage of patients who received one, two, three, or four doses of PA, or one, two, three, four, five, six, seven doses of AL. For vomited doses that were repeated the sum of both doses will be used.
- For patients in the PA group: Number and percentage of patients who vomited the first dose, the second dose, or the third dose.
- For patients in the AL group: Number and percentage of patients who vomited the first dose, the second dose, the third dose, the fourth dose, the fifth dose, or the sixth dose.
- Number and percentage of patients who received a repeated dose for the first dose and who vomited the repeated first dose.
- The total amount of dose of study drug administered expressed in mg/kg body weight, separately for artesunate, pyronaridine tetraphosphate, artemether, and lumefantrine. To calculate this, the total number of sachets/tablets taken by a patient will be multiplied by the strength and divided by the patient's body weight at baseline. For vomited doses that were repeated both the original and the repeated dose will be used.

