**Table 2.7.4-3 Study drug exposure**  
**Paediatric safety population**  
**(Page 1 of 1)**

| Variable/
Category          | Pyronaridine
artesunate
(N=xxx) |        | Artemether
lumefantrine
(N=xxx) |        |
|--------------------------------|---------------------------------------|--------|---------------------------------------|--------|
|                                | n                                     | (%)    | n                                     | (%)    |
| Total number of doses taken *  |                                       |        |                                       |        |
| One                            | xxx                                   | (xx.x) | xxx                                   | (xx.x) |
| Two                            | xxx                                   | (xx.x) | xxx                                   | (xx.x) |
| Three                          | xxx                                   | (xx.x) | xxx                                   | (xx.x) |
| Four                           | xxx                                   | (xx.x) | xxx                                   | (xx.x) |
| Five                           | xxx                                   | (xx.x) | xxx                                   | (xx.x) |
| Six                            | NA                                    |        | xxx                                   | (xx.x) |
| Seven                          | NA                                    |        | xxx                                   | (xx.x) |
| Eight                          | NA                                    |        | xxx                                   | (xx.x) |
| Dose repeated                  |                                       |        |                                       |        |
| Day 0 - Dose 1                 | xx                                    | (xx.x) | xx                                    | (xx.x) |
| Day 0 - Dose 2                 | NA                                    |        | xx                                    | (xx.x) |
| Day 1 - Dose 1                 | xx                                    | (xx.x) | xx                                    | (xx.x) |
| . . .                          |                                       |        |                                       |        |
| Dose vomited within 30 minutes |                                       |        |                                       |        |

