| Day 0 - Dose 1                 | xxx                                   | (xx.x) | xxx                                   | (xx.x) |
| Repeated dose                  | xxx                                   | (xx.x) | xxx                                   | (xx.x) |
| Day 0 - Dose 2                 | NA                                    |        | xxx                                   | (xx.x) |
| Repeated dose                  | NA                                    |        | xxx                                   | (xx.x) |
| . . .                          |                                       |        |                                       |        |

NA = not applicable

\* Original and repeat doses were taken into account.

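### Counting a vomited dose and its repeat as two doses puts some early stoppers in the full-course row, and no planned table shows how many children took every scheduled dose

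*SAP*

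**What the plan says.** SAP Section 7 asks for the number and percentage of children by number of doses received, with categories up to four for PA and up to seven for AL. Its rule for repeats is: "For vomited doses that were repeated the sum of both doses will be used".

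The shell of Table 2.7.4-3 has a block headed "Total number of doses taken", with the footnote "Original and repeat doses were taken into account". In this block PA runs to five doses (six to eight are marked not applicable) and AL runs to eight. Below it are two further blocks, one for doses repeated and one for doses vomited within 30 minutes. Both are set out by day and dose, and neither is crossed with the dose count.

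Section 7 does not state the number of scheduled doses outright. For PA it plans "Number and percentage of patients who vomited the first dose, the second dose, or the third dose". For AL the list ends with "the third dose, the fourth dose, the fifth dose, or the sixth dose". The schedule is therefore read here as three PA and six AL doses.

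Section 7 also defines a dosage variable: "The total amount of dose of study drug administered expressed in mg/kg body weight". For this variable the rule is: "For vomited doses that were repeated both the original and the repeated dose will be used". Table 2.7.4-4 carries the same footnote as Table 2.7.4-3.

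**The concern.** A reader of Table 2.7.4-3 will naturally take row Three (PA) or row Six (AL), and the rows above, as children who received the whole course. Under the adding rule that reading can fail. A child who stopped early but had enough repeats to make up the missed doses has the same count as a child who completed.

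The error runs in one direction: a repeat can only move a child up the table. The children affected are those who vomited, and in a safety summary for a paediatric granule formulation they are the group whose dosing history a reader will want to see clearly. Table 2.7.4-1 does not help, because it counts completion of the study and not of treatment.

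The text and the shell also differ on the highest possible count, so a programmer cannot follow both.

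**Working it through.** **Inputs.** Scheduled doses s = 3 for PA and 6 for AL, inferred from the vomiting bullets in Section 7. Highest counts are 4 (PA) and 7 (AL) in Section 7, and 5 and 8 in the Table 2.7.4-3 shell. The SAP gives no repeat rate and no fraction of a vomited dose retained; both are assumed below.

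**1. The plan's own ranges.** Highest count = s + number of repeats allowed.
- Section 7: 3 + 1 = 4 and 6 + 1 = 7, which allows one repeat.
- Shell: 3 + 2 = 5 and 6 + 2 = 8, which allows two repeats.

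Each range is consistent with the inferred schedule, but they are not consistent with each other.

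**2. What the full-course row contains.** Tabulated count = scheduled doses taken + repeats. With up to two repeats:
- PA, row Three: 3 + 0 or 2 + 1 (a child with 1 + 2 would need one dose repeated twice).
- AL, row Six: 6 + 0, 5 + 1 or 4 + 2.

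**3. Whether the other rows resolve it.** Take a hypothetical PA arm of 100 with row Two = 2, row Three = 94, row Four = 4, and six children repeating the first dose on Day 0. Suppose each of these six vomited that dose once and no repeat was vomited.
- Case A: both children in Two are 2 + 0; two children in Three are 2 + 1 and 92 are 3 + 0; the four in Four are 3 + 1. Repeats: 2 + 4 = 6. Completers: 92 + 4 = 96.
- Case B: both children in Two are 1 + 1; all 94 in Three are 3 + 0; the four in Four are 3 + 1. Repeats: 2 + 4 = 6. Completers: 94 + 4 = 98.

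The dose-count, first-dose repeat and first-dose vomiting rows are identical in the two cases. In both, 98 children show three or more doses; in case A two of them did not complete.

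**4. What can be recovered.** If each scheduled dose is repeated at most once, scheduled doses taken in the arm = total doses − total repeats. In the example, total doses = 2×2 + 94×3 + 4×4 = 302, and 302 − 6 = 296. The shortfall is 3×100 − 296 = 4 doses. A treated PA child can miss one or two doses, so non-completers lie between 4/2 = 2 and 4. That gives a bound of 96 to 98 completers, not the number.

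**5. The mg/kg variable.** Relative to retained dose, the excess is (s + k)/(s + k·f) − 1, with k repeats, f the fraction of a vomited dose retained, and equal dose size at each intake. For a full course and k = 1:

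| f | PA | AL |
|---|---|---|
| 0 | 4/3 − 1 = 33.3% | 7/6 − 1 = 16.7% |
| 0.5 | 4/3.5 − 1 = 14.3% | 7/6.5 − 1 = 7.7% |
| 1 | 0% | 0% |

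Relative to the amount administered, which is what the SAP says it reports, the excess is zero by definition.

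**6. Arm means at f = 0, full courses.** If a share q of children in each arm has one repeat, the mean rises by q/3 (PA) and q/6 (AL). For q = 5% this is 1.7% and 0.8%; for q = 15% it is 5.0% and 2.5%. If instead the repeat rate per scheduled dose, r, is equal, the rise is 3r/3 = r for PA and 6r/6 = r for AL. With r = 3% it is 3.0% in both arms.

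**The case against.** The counting rule is deliberate and is disclosed in a footnote under both tables. Only early stoppers who also had enough repeats are misplaced; other early stoppers stay in the lower rows. The arm-level total of scheduled doses can be recovered by subtraction if no dose was repeated more than once, and a zero shortfall would show that everyone completed. The safety population is anyone with at least one dose, and no adverse event or laboratory analysis is conditioned on dose count or mg/kg. The range mismatch is clerical. All of this stands and limits the weight of the point. The subtraction still gives only a bound on the number of completers, as step 4 shows.

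A reader might go further and infer that mg/kg exposure is overstated. The documents do not support that. Section 7 names the variable as the amount administered, and counting both intakes is correct for that quantity. The 33% and 17% figures hold only against retained dose with nothing retained, which the SAP neither states nor claims to measure. Replacing the administered figure as the main one would be a preference.

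A reader might also infer that the rule distorts PA twice as much as AL. That factor is a ratio of course lengths (six to three), exact only for full courses with nothing retained. It disappears from the arm means when the repeat rate per dose is equal, because AL has twice as many doses that can be repeated.

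**Conclusion.** The point holds for the dose count. As planned, row Three for PA and row Six for AL mix full courses with shortened courses made up by repeats, and no planned table gives the number of children who took every scheduled dose. The size depends on how many children both stopped early and had repeats, which the SAP does not allow one to estimate; in the worked example it is up to two children in 100. The conclusion rests on the inferred schedule of three PA and six AL doses, which both sets of stated ranges support.

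The disagreement between Section 7 and the shell on the highest count is a plain inconsistency.

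The mg/kg summary is not wrong, and no between-arm bias follows from the rule. This is a cheap improvement to a descriptive table.

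**What to change.** - In Section 7 and Table 2.7.4-3, tabulate scheduled doses taken, counting a vomited dose and its repeat once. State in a footnote how a dose is counted when its repeat was also vomited.
- Add a row for all scheduled doses taken.
- Keep repeats and vomiting in the rows already planned for them.
- Reconcile the dose-count ranges in Section 7 with those in the shell.
- Keep mg/kg administered as the main figure in Table 2.7.4-4. Optionally add a second line that leaves out vomited doses that were replaced, so that a reader can see the range between the two.

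The cost is a short change to the SAP text, a few lines of programming and a few extra table rows. The data are already needed for the existing repeat and vomiting rows.
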